### Randomization and blinding

Eligible patients will be randomized in a ratio of 3:1 to QFGKG group or placebo group, with stratification by participating center. A centralized randomization will be employed. The random coding of each center as well as the allocation sequence are generated electronically using SAS 6.12 software. Assignments are concealed in sequentially prepared coded, sealed, opaque envelopes, in which the corresponding intervention group of the randomization list will be found. A professional statistician who is independent of intervention and data collection is appointed to choose appropriate block length to ensure concealment. A group of research assistants who are not involved in recruitment, intervention or assessment of outcomes will prepare the envelopes. Staff responsible for recruitment is not allowed to take part in the group allocation. Only after the former participant is enrolled and his/her baseline testing is completed, the next envelope could be opened by researchers responsible for allocation. Participants will be randomized to the intervention group or the control group in line with numbered envelope under instructions from drug managers at each center. Blind codes along with random seeds and block length will be recorded in duplicate and delivered to Good Clinical Practice (GCP) Centre of West China Hospital and the sponsor for safekeeping. Patients and all engaged personnel including the sponsor remain blind to allocation and intervention throughout the whole process. Placebo will be packaged with imitative similarity in appearance, smell and taste with QFGKG. However, personnel who are designated to prepare drug packaging and labeling will not be blinded. The prepared emergency code-break envelope that contains allocation information, and emergency measures as well as contact details of the responsible department will be distributed to study centers along with drugs. Patients reported side effects will be recorded in the case report forms (CRFs) detailedly by physicians at visit 1 and visit 2. If an unpredictable severe adverse event happens, the chief investigator is qualified to open the emergency envelope and guide physicians to treat the patient according to emergency measures. The patient must be withdrawn and be followed up until he/she recuperates. In this case, the chief investigator should report the case to hospital ethical committee and drug administration agency. The broken code and reasons for unblinding should be recorded on CRF. Meanwhile, severe adverse event report form (SAERF) will also be completed. During the revealing, allocation information must not be disclosed to the patient and any third party.

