## Methods/Design

### Study designs

This trial is designed as a randomized, double-blind, placebo-controlled, parallel, phase III, superiority trial, with allocations stratified by participating centers and randomization performed as block at a ratio of 3:1, adhering to the recommendation of “CONSORT statement” [23] and “SPIRIT statement” [24]. As to the allocation ratio, generally speaking, for a superiority trial using placebo as a control intervention, 3:1 is recommended by Provisions for Drug Registration (http://www.sda.gov.cn/ypzcgl/ml.htm), taking into full consideration of statistical significance, ethical requirement and risk-cost relationship. This trial consists of two simultaneously conducted study parts (part A and part B), currently involving six participating centers across China: West China Hospital of Sichuan University, Tangdu hospital of The Fourth Military Medical University, Affiliated Hospital of Jiangxi University of TCM, the Second Affiliated Hospital of Tianjin University of TCM, Affiliated Hospital of Inner Mongolia Medical University, and the First Affiliated Hospital of Henan University of TCM. These centers were defined primarily geographically. In each participating center, a chief investigator will be appointed to be responsible for the whole clinical process (subject recruitment, intervention, follow-up, and data collection), adhering to the study protocol. All personnel involved in this trial will be trained prior to trial initiation. Training program is about study protocol and relevant skills, especially the skill of TCM syndrome differentiation. Staff placement and individual responsibility will also be elaborated in the training session. Besides, investigator’s brochure developed by the sponsor to facilitate the smooth running of the trial will also be provided. This protocol is designed largely depending on the results of previous phase II trial. Both study parts have been registered with Chinese Clinical Trial Registry (http://www.chictr.org). This protocol has two amendments. The schematic diagram and flow chart of study process are shown in Tables 1, 2 and Fig. 1.

**Table 1 Tab1:** Schematic diagram of part A

Phase	Supervision period			
Time-point	Baseline	Visit 1	Visit 2	Visit 3
Day	0	8 ± 1	15 ± 2	Follow-up
Basic history collection	×			
Informed consent	×			
Demographics	×			
Enrollment based on the inclusion/exclusion criteria	×			
Coexisting diseases or symptoms	×			
Concomitant treatments		×	×	

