Efficacy evaluation				
Cough symptom score	×	×	×	×
TCM syndrome score	×	×	×	
Safety evaluation				
Vital signs	×	×	×	
Blood routine and urine routine	×		×	
Liver function (ALT, AST, STB, ALP, γ-GT )	×		×	
Renal function (Cr, BUN)	×		×	
ECG	×		×	
Adverse events		×	×	
Screening tests				
CR	×			
BPT	×			
UPT (women of childbearing age)	×			
Other steps				
Randomization allocation	×			
Drug distribution	×			
Remaining drug count			×	
Patient record card distribution/recycling	×		×

**Table 2 Tab2:** Schematic diagram of part B

Phase	Supervision period			
Time-point	Baseline	Visit 1	Visit 2	Visit 3
Day	0	6 ± 1	11 ± 1	Follow-up
Basic history collection	×			
Informed consent	×			
Demographics	×			
Enrollment based on the inclusion/exclusion criteria	×			
Coexisting diseases or symptoms	×			
Concomitant treatments		×	×	
Efficacy evaluation				
Cough symptom score	×	×	×	×
Cough VAS score	×	×	×	
TCM syndrome score	×	×	×	
CQLQ	×		×	
Safety evaluation				
Vital signs	×	×	×	
Blood routine and urine routine	×		×	
Liver function (ALT, AST, STB, ALP, γ-GT )	×		×	
Renal function (Cr, BUN)	×		×	
ECG	×		×	
Adverse events		×	×	
Screening tests				
CR	×			
BPT	×			
UPT (women of childbearing age)	×			
Other steps				
Randomization allocation	×			
Drug distribution	×			
Remaining drug count			×	
Patient record card distribution/recycling	×		×

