### Interventions

After enrollment, eligible patients will be randomly assigned to receive twice daily QFGKG 12.0 g or twice daily dummy QFGKG (placebo) 12.0 g. The use of placebo as a comparator in this trial largely depends on empirical evidence [17, 28, 29] and Guidelines for Clinical Research of New Chinese Medicine [26]. Besides, the absence of generally recognized therapy and self-healing tendency of PIC also support the use of placebo. QFGKG and placebo in this trial are manufactured by Baotou TCM Co., Ltd. The Latin names, English names and Chinese Pinyin of the four herbs used in QFGKG are listed in Table 6. Both within-group changes and between-group changes are assessed across three time-points during treatment. As to the treatment duration, a longer (14 days) treatment in part A is conducted for the sake of more cured cases, while a shorter treatment (10 days) in part B is enough for monitoring noticeable changes in cough symptom score. A two-day follow-up will be conducted for all patients. At the initial drug dispensing stage, patients are advised to strictly follow protocol instructions, which will be reiterated at each study visit. Participants are requested to genuinely report their daily dosage of drugs that have been actually taken and to return unused ones to physicians at each study visit. Drug using and returning will be recorded on CRF by physicians. Unused drugs will be finally collected and counted by drug managers and then be destroyed by the sponsor at the end of the trial. All previous and concomitant treatments, including drug and non-drug therapies, taken one week before and during the intervention will be recorded on CRF. Concomitant treatment for comorbidities such as hypertension, diabetes and other chronic conditions are permitted during the intervention. Whereas, the use of antibiotics, Western or other antitussives, and non-drug cough suppressing therapies such as acupuncture and cupping are strongly discouraged to prevent potential systemic effects. Participating centers are required to record dropout cases and reasons, and also side effects happen during the intervention.

**Table 6 Tab6:** Latin name, English name and Chinese pinyin of the four herbs

Latin name	English name	Chinese pinyin
*Ephedra sinica Stapf*	Herba Ephedrae	Ma Huang
*Sinomenium acutum*	Caulis Sinomenii	Qing Feng Teng
*Stemona japonica (Blume) Miq.*	Radix Stemonae	Bai Bu
*Aster tataricus L.f.*	Aster tataricus	Zi Wan

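### Scheduled recording of adverse events and concomitant treatments stops at Visit 2, so non-severe events starting between Visit 2 and the Visit 3 follow-up (about 1 to 2 days) are not systematically captured

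*Protocol article*

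**What the plan says.** All references are to the protocol article.

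- **Randomization and blinding:** side effects that patients report "will be recorded in the case report forms (CRFs) detailedly by physicians at visit 1 and visit 2". For an unpredictable severe adverse event, the same section requires withdrawal, follow-up until recovery and a separate severe-event form. None of this is tied to a visit.
- **Tables 1 and 2 (Study designs):** in both parts the row "Adverse events" is marked at Visits 1 and 2 and blank at Visit 3. The concomitant-treatments row has the same pattern. The only item marked at Visit 3 is "Cough symptom score".
- **Visit days:** part A, "Day 0 8 ± 1 15 ± 2 Follow-up"; part B, "Day 0 6 ± 1 11 ± 1 Follow-up".
- **Interventions:** "a longer (14 days) treatment in part A is conducted for the sake of more cured cases"; part B treats for 10 days. Centers must record side effects that occur while patients are on the intervention. Concomitant treatments are recorded for the week before and during it. The section also states: "A two-day follow-up will be conducted for all patients".
- **Part B, Primary outcome:** the assessment two days after treatment is conditional, made only where needed.
- **Background and Statistical analysis:** safety is the fourth stated hypothesis, and the proportions of patients with adverse events are to be compared between groups.

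**The concern.** The trial plans a contact after treatment and uses it for efficacy but not for safety. The article prints the full schedule and names the visits in the text, so this is a stated rule and not a detail lost when the protocol was condensed.

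What is at stake is the completeness of the adverse-event count behind a stated hypothesis. The Discussion names the lack of follow-up as a limitation of the phase II trial. The follow-up added here leaves that limitation in place for safety. A second, smaller consequence is that the Visit 3 cough score has no scheduled record of any antitussive taken since Visit 2.

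**Working it through.** The plan gives no figure to reproduce. The check places the last adverse-event entry relative to the last dose and to Visit 3.

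**Inputs.** Visit 2 is day 15 ± 2 in part A (Table 1) and day 11 ± 1 in part B (Table 2). Treatment lasts 14 days in A and 10 days in B (Interventions). Follow-up is two days (Interventions). The first dosing day is not stated; day 1 is assumed, with day 0 as the alternative.

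**Step 1: Visit 2 relative to the last dosing day.** Offset = Visit 2 day − last dosing day.

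| Part | Dosing starts | Last dosing day | Visit 2 early | Visit 2 nominal | Visit 2 late |
|---|---|---|---|---|---|
| A | day 1 | 14 | 13 − 14 = −1 | 15 − 14 = +1 | 17 − 14 = +3 |
| A | day 0 | 13 | 13 − 13 = 0 | 15 − 13 = +2 | 17 − 13 = +4 |
| B | day 1 | 10 | 10 − 10 = 0 | 11 − 10 = +1 | 12 − 10 = +2 |
| B | day 0 | 9 | 10 − 9 = +1 | 11 − 9 = +2 | 12 − 9 = +3 |

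At nominal timing, Visit 2 comes after the last dose in both parts. The only negative entry is part A with dosing from day 1 and Visit 2 on day 13: one dosing day would then follow the last scheduled adverse-event entry. That does not fit the instruction to record side effects arising during the intervention.

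**Step 2: days from Visit 2 to Visit 3.** The article does not say where the two-day follow-up starts.

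- Counted from Visit 2: 2 days.
- Counted from the last dose, with dosing from day 1 and nominal timing: 2 − 1 = 1 day in either part.

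The stretch without scheduled recording that Visit 3 could cover is therefore about 1 to 2 days.

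**Step 3: what has no scheduled entry in that stretch.** Severe events have their own form and are followed to recovery. Laboratory tests and ECG are done at Visit 2, the same visit as the last adverse-event entry, and are listed as safety outcomes in their own right. What remains is non-severe events that begin after Visit 2, together with concomitant treatments started after it.

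**The case against.** The strongest defence is that the rule is coherent. The text, both tables and the Interventions section all point to collection during treatment, and at nominal timing Visit 2 covers the whole treatment period and about a day beyond it. On that view, recording for one or two further days is a preference. Much of this stands: no stated figure is affected, and apart from the early edge of the part A window there is no contradiction about when events are recorded. It does not explain why a contact promised to all patients should leave out a question that costs almost nothing.

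A reader might infer more than the article supports:

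- **That all events after the last dose are lost.** They are not. Visit 2 nominally follows the last dose, so the gap begins at Visit 2.
- **That Visit 2 laboratory and ECG findings have no recording point.** Adverse events are entered at that same visit, and Safety outcomes makes these results outcomes themselves. No turnaround time is given, and nothing says the CRF closes to such entries. How abnormal results are followed up may be set out in the full protocol.
- **That severe events go unrecorded.** Their separate form and follow-up have no visit limit.
- **That the share of uncovered days measures the share of missed events.** It does not. These are mostly days off drug, and no event rate is given.

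Two practical objections also stand. Visit 3 may not take place for everyone in part B, where the assessment is conditional, and the mode of contact is not stated. If so, the change adds contacts as well as CRF lines. And the Trial status section reports 318 of 480 patients already included, so a change from then on would reach at most 480 − 318 = 162 later patients, plus any still under observation.

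**Conclusion.** The point holds in a narrow form. Adverse events and concomitant treatments are scheduled only to Visit 2, and Visit 3 takes a cough score alone, so non-severe events starting after Visit 2 are not systematically captured. The gap is about 1 to 2 days, depending on whether the follow-up is counted from the last dose or from Visit 2. In part A, one dosing day could also be uncovered if dosing starts on day 1 and Visit 2 falls on day 13; with dosing from day 0 that does not arise.

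The effect on adverse-event proportions, or on the difference between groups, cannot be estimated from the article. The same schedule applies to both groups, so the visible problem is incomplete ascertainment and not a demonstrated bias. Severity is low: a cheap improvement for a stated safety hypothesis.

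**What to change.** 1. In Tables 1 and 2, mark adverse events and concomitant treatments at Visit 3.
2. In Randomization and blinding, extend the sentence on side effects to visits 1, 2 and 3. In Interventions, extend the recording of side effects and concomitant treatments to the follow-up contact.
3. Reconcile Interventions, which promises the follow-up to every patient, with the part B primary outcome, which makes it conditional. The change works only if Visit 3 takes place for everyone. If the contact depended on how the cough was doing, adverse-event capture would depend on response and could then differ between groups.
4. Report adverse events to Visit 2 and to Visit 3 separately, because patients enrolled before the change would have them recorded only to Visit 2.

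**Cost.** One or two CRF lines at a planned contact, and a short amendment. If Visit 3 is in practice conditional in part B, there are also extra contacts for patients who would not otherwise have had one. The length of adverse-event observation would differ between earlier and later patients. Randomization is blocked within center, so both groups should be affected in about the 3:1 ratio, and the separate report to Visit 2 keeps one window common to all patients.

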
### Sample size

The latest edition of Provisions for Drug Registration issued by CFDA recommends a minimum number of 300 for subjects enrolled in the trial group in a phase III clinical trial. Sample size calculation of this trial results in 24 patients in total for part A (18 in the QFGKG group and 6 in the placebo group) and 56 patients in total for part B (42 in the QFGKG group and 14 in the placebo group), respectively. Obviously, the calculated patient number in the QFGKG group is much smaller than the recommended one. Given the above, we set the sample size according to the Provisions for Drug Registration. 480 patients in total would be included, with 360 being assigned to the QFGKG group and 120 being assigned to the placebo group, considering a maximal dropout rate of 20 %. Calculation assumed an 80 % power for a two-sided log-rank test at a 5 % significance level.

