Intervention duration		Formula: the last day using test drugs-the first day using test drugs + 1	T-test/Wilcoxon rank sum test
Primary			
Time to cough resolution	improvement occurred		Kaplan-Meier method/Log-rank test
Cough symptom score	improvement occurred		T-test/Wilcoxon rank sum test
Secondary			
VAS score	improvement occurred		T-test/Wilcoxon rank sum test
TCM symptom score	improvement occurred		T-test/Wilcoxon rank sum test
TCM curative effect	improvement occurred	Percent and cases of four grades: complete recovery, excellent effect, modest effect and no effect	Cochran-Mantel-Haenszel Chi-squared test
CQLQ score	improvement occurred	Questionnaire	T-test/Wilcoxon rank sum test
Cough disappearance rate	improvement occurred		CMH Chi-squared test
Time to cough relief	improvement occurred		Kaplan-Meier method/Log-rank test

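### The 20% dropout allowance is computed the wrong way (360 less 20% leaves 288, not 300), and the one stated power basis, a log-rank test, does not fit part B's primary analysis

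*Protocol article*

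**What the plan says.** All of the sizing is in the Sample size section of the protocol article. It cites the drug registration provisions, which it says "recommends a minimum number of 300 for subjects enrolled in the trial group in a phase III clinical trial". It reports calculated sizes of "24 patients in total for part A (18 in the QFGKG group and 6 in the placebo group") and 56 for part B (42 and 14). Because these fall well below the recommended number, it states: "we set the sample size according to the Provisions for Drug Registration". The resulting plan is a total of 480, "with 360 being assigned to the QFGKG group and 120 being assigned to the placebo group, considering a maximal dropout rate of" 20%. The section closes with one sentence on the basis of the calculation: 80% "power for a two-sided log-rank test" at the 5% level. That sentence is not limited to either part.

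Under Outcome measures, part A's primary outcome is time to cough resolution and part B's is the cough symptom score. In Table 8 (Statistical analysis), the primary time to cough resolution is analysed by Kaplan-Meier and log-rank methods, and the primary cough symptom score by "T-test/Wilcoxon rank sum test".

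**The concern.** There are two separate points.

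- **Dropout allowance.** The 300 figure is the only basis for the size of the trial. Of the numbers in the section, 360 is the one meant to carry it through a stated maximal loss. If the inflation is done the wrong way, the allowance does not deliver what it appears to promise. Anyone monitoring retention against a 20% ceiling would take 300 completing patients to be safe when they are not.
- **Basis of the calculation.** The design rests on each part being built around its own primary outcome. A single log-rank basis for both calculated sizes does not fit part B, whose primary analysis compares scores. Part B's 56 was therefore either sized for a different kind of outcome or has its basis misdescribed. The article does not let a reader tell which.

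**Working it through.** **Inputs (Sample size section unless noted).** Minimum in the QFGKG group: 300. Planned: 360 QFGKG, 120 placebo, 480 in total. Maximal dropout: 20%. Allocation: 3:1 (Randomization and blinding). Calculated sizes: 24 (18:6) and 56 (42:14). Stated basis: 80% power, two-sided 5%, log-rank. Size per part: 240, as 180:60 (Abstract).

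**Step 1. Reproduce the plan's figure.** Multiplying by one plus the dropout rate: 300 × (1 + 0.20) = 360. At 3:1, placebo = 360/3 = 120 and the total is 480. This matches exactly.

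**Step 2. Apply the stated dropout to 360.** 360 × (1 − 0.20) = 288 completing QFGKG patients, and 300 − 288 = 12 short.

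**Step 3. Inflate correctly.** n/(1 − d) = 300/0.80 = 375 QFGKG. At 3:1, placebo = 375/3 = 125 and the total is 500.

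**Step 4. Find what 360 tolerates.** 1 − 300/360 = 0.167, so 300 complete only if dropout is at most 16.7%. Put another way, the 60 patients added are 20% of 300 but only 16.7% of the 360 enrolled, and a dropout rate is a share of those enrolled.

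**Step 5. Set the stated basis against the primary analyses.**

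| | Calculated size | Stated basis | Primary outcome | Test in Table 8 |
|---|---|---|---|---|
| Part A | 24 (18:6) | log-rank, 80% | time to cough resolution | log-rank |
| Part B | 56 (42:14) | log-rank, 80% | cough symptom score | t-test/Wilcoxon |

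Part A agrees and part B does not. The 24 and 56 cannot be reproduced, because the article gives no effect size for either.

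**Step 6. Illustration of why part B's basis matters.** The normal quantiles sum to 1.960 + 0.842 = 2.802. The event fractions are assumptions, since the article states none.

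- Part B's 56 read as a log-rank size: HR = exp(2.802/√(0.1875 × events)), where 0.1875 = 0.75 × 0.25. This gives about 2.4 if all 56 have the event and 3.4 if half do.
- Part B's 56 read as a t-test size: 2.802 × √(1/42 + 1/14) = about 0.86 SD.

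These are different planning assumptions on different scales, and the article does not say which was used.

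**Step 7. Optional context at 180:60 per part, before any loss.** Part B: 2.802 × √(1/180 + 1/60) = about 0.42 SD. Part A: a hazard ratio of about 1.5 (all 240 with events) to 1.8 (half with events).

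**The case against.** **A reader might infer that the regulatory minimum is missed.** The document does not support this. The minimum is described as a recommendation about subjects enrolled, and 360 enrolled exceeds 300 at any dropout. This objection stands in full. It does not rescue the allowance: if 300 means enrolment, dropout is irrelevant to it and the extra 60 patients have no stated purpose; if 300 means patients remaining, 360 is too few at 20%.

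**Dropouts are not all lost to analysis.** The Full Analysis Set keeps every randomised patient who took study drug, with last observation carried forward for missing primary values. This also stands: 288 counts completers and is not the size of the Full Analysis Set. The Per Protocol Set, in which the primary outcome is also analysed, is where such losses would show.

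**A reader might infer that the article claims 80% power for 240 or 480 patients, or that its power statement is false.** It does neither. The sentence describes the calculation, and the section says openly that the calculated sizes were replaced by the regulatory number. Nor does the larger size cost power. For effects back-solved from the calculated sizes (hazard ratio about 3.75 for part A if all 24 have events; about 0.87 SD for part B), power at 240 per part, or at 192 after 20% loss, exceeds 99.9%. For part A that holds even if only half have events.

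**The log-rank sentence may be condensed and meant for part A only.** This is plausible, because two different totals suggest two calculations, and effect sizes are details that an article may leave to the full protocol. It is therefore not shown that part B was sized with the wrong test. What stands is that the sentence, as printed, covers both sizes and does not fit part B.

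**Conclusion.** The point holds in two limited parts.

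1. The dropout allowance multiplies by 1.2 where it should divide by 0.8. At the stated maximum, 288 QFGKG patients complete, 12 fewer than 300; 375 would be needed to keep 300, and 360 does so only up to 16.7% dropout. This rests on the 300 being meant to remain after loss. The allowance implies that reading, but the text does not state it.
2. The only stated basis for the calculated sizes is a log-rank test, which does not match the t-test or Wilcoxon test set for part B's primary outcome. This rests on the documents' wording alone.

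The rest of the sizing is consistent: 360 + 120 = 480, and 18:6, 42:14 and 360:120 are all 3:1. Neither part of the point changes the analysis or the error rate, or shows a loss of power. Both should be corrected, because the trial relies on these figures and the remedy is wording.

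**What to change.** No extra enrolment is needed.

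- **Dropout.** Either state that 360 keeps at least 300 completing QFGKG patients up to 16.7% dropout and leaves 288 at 20%, or state that the 300 refers to enrolment only and that the 20% is not meant to protect it.
- **Basis.** Limit the log-rank sentence to part A. For part B's 56, add the basis actually used, in terms of the Table 8 test: the assumed difference and SD for a t-test, or the equivalent for the Wilcoxon test. If 56 was in fact derived from a log-rank calculation, say so and note that it does not correspond to the primary analysis.
- **Optional.** Add the detectable effect per part at 180:60 (about 0.42 SD for part B; a hazard ratio of about 1.5 to 1.8 for part A), with the assumed 100% to 50% event range labelled as an assumption. The per-centre numbers under Study participants (60 in part A, 80 in part B) would give 360 and 480 over six centres, not 240 each, so settle the size per part before quoting these.

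The cost is a few sentences, and the stated dropout tolerance becomes slightly less favourable. Part B's basis has to be retrieved from the original calculation.
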